**Figure 1 figure1:**
[figure not shown]
Flowchart showing study design. DC/TMD: Diagnostic Criteria for Temporomandibular Disorders; EMG: electromyography; TMD: temporomandibular disorder.

### Outcomes

The outcome measurements will be made by an examiner calibrated according to the guidelines of DC/TMD criteria. The DC/TMD instruction video has been peer-reviewed and published [22]. Self-study guidelines and description of supervised skill development have also been described. The outcome measurements will be made at baseline and at the time points of 24 hours, 7 days, 28 days, and 3 months.

#### Primary Outcome Measurements

##### Pain

Pain will be measured using the visual analog scale (VAS) for pain. The pain VAS is a unidimensional single item measure of pain intensity [23], which has been widely used in diverse adult populations. Using a ruler, the score is determined by measuring the distance (mm) on the 10-cm line between the “no pain” anchor and the patient’s mark, providing a range of scores from 0 to 100 [24].

For pain intensity, the scale is most anchored by “no pain” (score of 0) and “pain as bad as it could be” or “worst imaginable pain” (score of 100 on a 100-mm scale). The following cut points on the pain VAS will be used: no pain (0-4 mm), mild pain (5-44 mm), moderate pain (45-74 mm), and severe pain (75-100 mm) [25].

##### Electromyography

The EMG of the masseter and the temporalis will be recorded with the individuals seated with their heads guided in the Frankfurt horizontal plane. The masseter and temporal anterior muscles will be examined with surface electrodes at an interelectrode distance of 20 mm positioned on the muscle bellies parallel to the muscle fibers (“temporal anterior: vertically along the anterior muscular margin around the coronal suture; masseter: parallel to the muscle fibers, with the upper pole of the electrode at the intersection between the tragus-labial commissure and the exocanthion-gonion lines”) [26]. Reference electrodes will be applied in positions “inferior and posterior to the right ear” [27].

#### Secondary Outcome Measurements

##### Pain Drawing

The pain reported in distinct body regions, especially if related to known regional disorders (eg, headache, back pain, pelvic pain, or neck pain), can be summarized as a count variable. Extent of pain can be computed as percent of the body area [28].

##### Graded Chronic Pain Scale, Version 2.0

This scale [29] includes three items for pain intensity, four items for function, and one item for number of days of pain. *Characteristic pain intensity* is the computed mean of items 2 to 4 (pain right now, worst pain, average pain) multiplied by 10. The *interference score* is the computed mean of items 6 to 8 (daily activities, social activities, work activities) multiplied by 10. The total disability points are the sum of points for disability days + points for interference score. Based on the scores, chronic pain is graded as 0 (none), I (low-intensity pain, without disability), II (high-intensity pain, without disability), III (moderately limiting), and IV (severely limiting).

##### Jaw Functional Limitation Scale

This scale [30] with 20 items is used to calculate a single global score of “jaw functional limitation” by computing the mean of the available items. Subscale scores for each type of functional limitation are computed as follows:

Mastication: mean of items 1 to 6Mobility: mean of items 7 to 10Verbal and nonverbal communication: mean of items 13 to 20

##### Oral Behaviours Checklist

Scoring can be computed as the sum of the number of items with nonzero response. Based on comparison of individuals with chronic TMD versus those without TMD, an Oral Behaviours Checklist summary score of 0 to 16 appears to represent normal behaviors, while a score of 17 to 24 occurs twice as often in those with TMD, and a score of 25 to 62 occurs 17 times more often. As a risk factor for TMD, only a score in the 25 to 62 range contributes to TMD onset [31].

##### Patient Health Questionnaire-9: Depression

The Patient Health Questionnaire (PHQ)-9 [32] is comprised of 9 items assessing depressed mood. A total sum score is computed. Scores of 5, 10, 15, and 20 represent cut points for mild, moderate, moderately severe, and severe depression, respectively.

##### Patient Health Questionnaire-15: Physical Symptoms

The PHQ-15 [33] is comprised of 15 items and assesses nonspecific physical symptoms, also referred to as functional symptoms or medically unexplained symptoms. Items are scored by adding the individual responses. A total sum score is computed. Scores of 5, 10, and 15 represent cut points for low, medium, and high physical symptoms, respectively.

##### General Anxiety Disorder-7: Anxiety

The General Anxiety Disorder-7 [34] is comprised of 7 items assessing anxious mood and behavior. A total sum score is computed. Scores of 5, 10, and 15 represent cut points for mild, moderate, and severe anxiety, respectively.

### Participation Timeline

Each eligible patient will be participating in the trial for 3 months, 1 year from their visit (baseline). The total number of visits will depend on the study arms to which the participants are allocated, but the outcome measurements will be recorded at 5 visits (baseline, 24 hours, 1 week, 28 days, and 3 months; Figure 2 and Table 1).

**Figure 2 figure2:**
[figure not shown]
Schedule of enrollment, interventions, and assessment. DC/TMD: Diagnostic Criteria for Temporomandibular Disorders; EMG: electromyography.

**Table 1 table1:** Participation timelines.

Procedures		1^a^ (0 weeks)	2^b^ (2 weeks)	3 (24 hours)	4 (7 days)	5 (28 days)	6 (3 months)
Prescreening consent		Yes	No	No	No	No	No
Informed consent		Yes	No	No	No	No	No
Oral examination		Yes	No	No	No	No	No
Eligibility assessment		Yes	No	No	No	No	No
Allocation to study arms		Yes	No	No	No	No	No
**Prosthetic intervention**							
	Group 1	No	Yes	Yes	Yes	Yes	Yes
	Group 2	No	Yes	Yes	Yes	Yes	Yes
	Group 3	No	Yes	Yes	Yes	Yes	Yes
Compliance		Yes	No	No	No	No	No
Assessment of DC/TMD^c^, EMG^d^, review of prosthesis		Yes	Yes	Yes	Yes	Yes	Yes
Adverse event assessments		No	Yes	Yes	Yes	Yes	Yes

^a^It may be single or multiple based on patient-informed consenting process.

^b^It may be multiple based on the type of prosthesis being delivered.

^c^DC/TMD: Diagnostic Criteria for Temporomandibular Disorders.

^d^EMG: electromyography.

### Sample Size

The activity of masticatory muscle (mean and SD) while chewing, estimated by EMG, reflects the TMD in a patient [35]. With a power of 80%, alpha error of .05, and effect size of 0.77, the minimum sample size estimated for each group was 22. Considering attrition and the inclusion of various variables (edentulousness location, etc), we increased the sample to 50 for each interventional group. The sample size of 50 will have a minimum of 20 patients with edentulous maxilla and 20 patients with edentulous mandible for intervention groups 1 and 2. The total sample size for the study is 300 with 150 for the interventional group and 150 for the control group. Please refer to Table 2 for the sample breakdown.

**Table 2 table2:** Sample size breakdown.

			Group 1: removable partial denture, n		Group 2: removable partial denture with stabilization splint, n		Group 3: removable complete denture, n		Total, n
**Intervention**			50		50		50		150
	Patients with edentulous maxilla	20		20		20			
	Patients with edentulous mandible	20		20		20			
	Total	40		40		40			
	Females	20		20		20			
	Males	20		20		20			
	Total	40		40		40			
**Control**			50		50		50		150
	Patients with edentulous maxilla	20		20		20			
	Patients with edentulous mandible	20		20		20			
	Total	40		40		40			
	Females	20		20		20			
	Males	20		20		20			
	Total	40		40		40			
Sample per group			100		100		100		300

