**Methods:**

In this randomized controlled trial, 300 patients diagnosed with TMD will be grouped into one of the three interventional groups based on the type of their edentulous state. The interventional groups are (1) partially edentulous arch: Kennedy Class I and II (prosthetic rehabilitation without splint); (2) partially edentulous arch: Kennedy Class III and IV (prosthetic rehabilitation with a splint); and (3) completely edentulous arches (prosthetic rehabilitation without splint). All three of the mentioned interventional groups have corresponding control groups that will receive symptomatic treatment and comprehensive counseling. The measured primary outcomes are pain and electromyogram, and the secondary outcomes include pain drawing, Graded Chronic Pain Scale, Jaw Functional Limitation Scale, Oral Behaviours Checklist, depression, physical symptoms, and anxiety. The outcome measurements will be recorded at baseline and at the end of 24 hours, 7 days, 28 days, and 3 months.

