#### Primary Objective

The primary objective is to determine the effectiveness of prosthetic rehabilitation in the reduction of pain in edentulous patients with TMD.

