**Subgroup analysis**							
	Effectiveness of reduction of pain: between group 1, group 2, and group 3	Intervention improved outcome from baseline to 12 months		Per person reduction of VAS score and GCPS (proportion or mean)		Regression methods with appropriate interaction term	
	Between posterior teeth rehabilitation vs anterior teeth rehabilitation	Number of teeth affects effectiveness of outcome		Per person reduction of VAS score and GCPS (proportion or mean)		Chi-square methods	
	Upper vs lower teeth	Position of edentulism affects the effectiveness outcome		Per person reduction of VAS score and GCPS (proportion or mean)		Chi-square methods	
	Duration of edentulism	Duration of edentulism affects pain outcome		Per person reduction of VAS score and GCPS (proportion or mean)		Chi-square methods	
	Number of quadrants	Number of quadrants affects the effectiveness outcome		Per person reduction of VAS score and GCPS (proportion or mean)		Chi-square methods	

^a^In all analyses, results will be expressed as coefficient, SEs, corresponding 95%, and associated *P* values. Goodness of fit will be assessed by examining the residuals for model assumptions and chi-square tests for goodness of fit.

^b^VAS: visual analog scale.

^c^GCPS: Graded Chronic Pain Scale.

^d^ANOVA: analysis of variance.

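### The sample size is worked out for EMG, with sidedness unstated, so the 80% power does not describe the pain test; EMG is also a primary outcome with no listed analysis

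*Protocol article*

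**What the plan says.** All references are to the protocol article.

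- **Sizing variable.** The Sample Size section starts from EMG: "The activity of masticatory muscle (mean and SD) while chewing, estimated by EMG, reflects the TMD in a patient". It then gives "With a power of 80%, alpha error of .05, and effect size of 0.77, the minimum sample size estimated for each group was 22". It raises this to 50 for each intervention group, citing attrition and further variables, with 50 in each matching control group (150 vs 150, total 300). It names neither the test nor its sidedness.
- **Objective.** "The primary objective is to determine the effectiveness of prosthetic rehabilitation in the reduction of pain in edentulous patients with TMD". The Research Question and Hypothesis also concern pain only, and Data Monitoring names reduction in pain as the one primary end point for the interim analysis.
- **Primary outcomes.** The abstract says "The measured primary outcomes are pain and electromyogram", and Primary Outcome Measurements lists both.
- **Analysis.** Statistical Methods opens with an analysis of variance of pain reduction. Every row of Table 3, the list of proposed analyses, uses the VAS and the Graded Chronic Pain Scale; no row uses EMG. Its footnote a reads in part "In all analyses, results will be expressed as coefficient, SEs, corresponding 95%, and associated" P values.
- **Loss to follow-up.** Data Collection Methods projects at most 5% a year.

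**The concern.** A power statement tells the reader what difference the trial can detect on the outcome that decides its conclusion. Here it concerns a different outcome. Without a VAS difference or SD, nobody can say whether 50 vs 50, or 150 vs 150, is adequate for pain. If the pain result is null, the 80% could be cited as evidence of adequate power when it is nothing of the kind.

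Two further defects sit alongside this. The figure of 22 does not follow from its stated inputs under the two-sided testing that Table 3 implies. And EMG, which justifies the sample size and is called primary, has no listed analysis, while the article elsewhere speaks of a single primary end point. As written, either outcome could later be presented as the primary result.

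**Working it through.** **Inputs.** Effect size d = 0.77, alpha .05, power 80%, stated minimum 22, planned 50 per arm and 150 vs 150 overall (Sample Size); equal allocation (Sequence Generation); loss of at most 5% (Data Collection Methods). Assumption: 0.77 is a standardised difference between two independent means, since the mean and SD behind it are not given.

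**1. Reproducing 22.** The normal approximation is n per group = 2 × [(z_alpha + z_power) / d]².

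- One-sided: 2 × [(1.645 + 0.842) / 0.77]² = 20.9. The exact t-test gives 21.6, rounded up to **22**, the stated figure.
- Two-sided: 2 × [(1.960 + 0.842) / 0.77]² = 26.5. The exact t-test gives 27.5, rounded up to **28**.
- Rounding of the effect size does not explain the gap: with d from 0.765 to 0.775 the two-sided t-test still needs 28.
- Other readings miss. A paired t-test gives 12 (one-sided) or 16 (two-sided). ANOVA with f = 0.77 gives about 7 per group for three groups and 5 for six. A three-group ANOVA with f = 0.77/2 gives 23, but halving d is the two-group conversion and does not apply to three groups.

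**2. Two-sided power for d = 0.77 (t-test).**

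| n per arm | Power |
|---|---|
| 22 | 70% |
| 28 | 81% |
| 47 (50 less 5%, rounded down) | 96% |
| 50 | 97% |

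With 5% loss the two-sided minimum becomes 28 / 0.95 = 29.5, so 30. Fifty per arm covers this.

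**3. What the fixed sample can detect on pain.** The document gives no pain effect, so the calculation is turned round. With 80% power and two-sided .05, the smallest detectable effect is:

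- 50 vs 50: 0.57 SD (0.58 SD at 47 vs 47);
- 150 vs 150: 0.325 SD.

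If the SD of the VAS outcome is 20 to 30 mm (assumed), this is 0.566 × 20 = 11 mm to 0.566 × 30 = 17 mm within one edentulism group, and 0.325 × 20 = 6.5 mm to 0.325 × 30 = 10 mm overall.

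Two-sided power for assumed pain effects:

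| Pain effect (SD) | 50 vs 50 | 150 vs 150 |
|---|---|---|
| 0.3 | 32% | 74% |
| 0.4 | 51% | 93% |
| 0.5 | 70% | 99% |
| 0.6 | 84% | >99% |

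**4. Two primary outcomes.** If each is tested at two-sided 5% and a positive result on either counts:

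- independent tests: 1 − 0.95² = 9.75%;
- correlation 0.5 (assumed, bivariate normal): 9.07%.

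With alpha split to .025 each, d = 0.77 needs 33.4, so 34 per group by two-sided t-test, and 50 per arm gives 94% power.

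**The case against.** **Nobody will enrol 22.** This stands. At 50 per arm the EMG effect has 97% two-sided power. A reader might infer from the one-sided match that the trial is under-powered; for the effect it was sized on, it is not.

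**One-sidedness is an inference.** This also stands. The article names no test, and the source of 0.77 is not visible. The hypothesis is directional, so a one-sided calculation would be an undeclared choice, not a slip of arithmetic. A two-sided comparison adjusted for a baseline value could also give 22 with a suitable correlation (about 0.46), though nothing in the article indicates this. What remains is that the figure does not fit the ANOVA, chi-square tests and 95% intervals of Table 3, which are conventionally two-sided.

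**The minimum cells.** A reader might set "a minimum of 20 patients with edentulous maxilla and 20 patients with edentulous mandible" against the 22 and conclude that these cells fall below the plan's own minimum. The document does not support that. The 20s fix the composition of each group of 50. They are not presented as powered units, and the upper-versus-lower row in Table 3 is a subgroup analysis that is not confined to one such cell.

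**Detail may be left to an SAP.** This is fair for a full multiplicity scheme. It does not answer the mismatch inside the article, which prints its own list of proposed analyses, leaves one of its two primary outcomes out, and elsewhere names pain alone as the primary end point.

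**Conclusion.** The concern holds in a limited form. The lasting defect is that the power statement is for EMG and the trial's question is pain. The 80% does not describe the pain test, and power for pain cannot be derived from the document. At 50 vs 50 it falls below 80% for any pain effect under about 0.57 SD; at 150 vs 150 the limit is about 0.325 SD. Whether that is adequate depends on a pain difference and SD that the article does not give.

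The sidedness point is a correction to a stated number: 28 instead of 22 under two-sided testing, with 70% power at 22. It rests on reading 0.77 as a two-sample standardised difference, and it has no consequence for enrolment on the EMG effect.

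The status of EMG is inconsistent within the document. The 9.1 to 9.8% error rate applies only if both outcomes are tested at 5% and either may carry the claim. The millimetre figures depend on the assumed SD of 20 to 30 mm.

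This should be corrected, but it does not invalidate the design.

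**What to change.** 1. In Sample Size, state two-sided alpha and the test. Restate the minimum as 28 per group (about 30 with 5% loss), noting that 50 per arm covers it.
2. Add the pain effect detectable with 80% power at the fixed sample: 0.57 SD at 50 vs 50 (0.58 SD after 5% loss) and 0.325 SD at 150 vs 150. Convert these to VAS millimetres with a stated SD, and say which comparison is the main one.
3. Name VAS pain as the single primary outcome, in line with the Objectives and Data Monitoring, at one time point. First reconcile the texts: the abstract, Outcomes, the outcome visits in Participation Timeline, and Strengths and Limitations use 3 months; Table 3 and Data Monitoring use 12 months.
4. Make EMG secondary with its own row in Table 3. If it stays co-primary, give it a row and split alpha at .025 each (34 per group needed, 94% power at 50 per arm for d = 0.77). The detectable pain effects in item 2 must then be recalculated at .025 and will be larger.

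**Cost.** Items 1 and 2 are wording and add no participants. Items 3 and 4 are more than wording. Recruitment began in May 2021, so changing an outcome's primary status needs an IRB-approved amendment under Protocol Amendments and a registry update, both made before outcome data are analysed. Keeping EMG co-primary leaves both outcomes' status unchanged, at the price of a stricter threshold for pain.

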### Recruitment

The adults visiting for routine dental care prosthodontics, Amrita School of Dentistry or at Amrita Urban Dental Health Centre will be recruited for the study. On examination, if the patient is found to satisfy the inclusion criteria, then they will be given options for the management of TMD by prosthetic rehabilitation or by splints. If the patient opts for prosthetic rehabilitation, then an option of participation in the trial will be explained, and the consenting process is followed. In case the patient declines to participate in the trial, the missing teeth will be managed according to the standard protocol of the department.

### Sequence Generation

The selected patient for trial will be randomly allocated to either the intervention arm or the control arm of their group, as per computer-generated randomization, schedule stratified, based on the type of group it belongs. The selected individuals will be allocated in equal probabilities to the intervention and control groups by stratified randomization. Stratified randomization is achieved by performing a separate randomization procedure within each of the two strata of participants. This will ensure that the numbers of participants receiving each intervention are closely balanced within each stratum. Treatment assignments are then made from separate randomization lists created in advance of the trial for each stratum.

### Allocation Concealment Mechanism

Allocation concealment will be ensured, the randomization code will not be released until the patient has been recruited into the trial, which takes place after all baseline measurements have been completed. The randomized codes, kept in a sealed cover at each clinic, will assign the patient to the intervention at baseline visit. The statistician will design the randomization schedule.

### Implementation

The randomization will be conducted by a statistician to manage the data, and the statistician will be blind against the study condition. The randomization list will remain with the doctoral committee for the whole duration of the study. Thus, randomization will be conducted without any influence of the dentist and hygienist.

### Blinding

Due to the obvious nature of the treatment, neither the treating dentist or patients are blinded; patients are only randomly allocated to the intervention. However, the data analyst or statistician will be blinded during the statistical process.

### Data Collection Methods

Each personnel will be trained centrally for the study requirements, standardization of examination and assessment of the outcomes and counselling for adherence, and the eliciting of information from study participants in a uniform reproducible manner. The data to be collected and the procedures to be conducted at each visit will be reviewed in detail. Each of the data collection forms and the nature of the required information will be discussed in detail on an item-by-item basis. Entering data forms, responding to data discrepancy queries, and general information about obtaining research quality data will also be covered during the training session. Once an individual is enrolled or randomized, the study site will make every reasonable effort to follow the individual for the entire study period of 12 months. It is projected that the rate of loss-to-follow-up on an annual basis will be at most 5%.

### Retention

Everyone has the right to withdraw from the trial at any time. In addition, the treating dentist may discontinue an individual from the trial at any time if they consider it necessary for any reason, including:

Ineligibility (either arising during the trial or retrospectively having been overlooked at screening)Significant protocol deviationSignificant noncompliance with treatment regimen or trial requirementsAn adverse event that requires discontinuation of the trial or results due to inability to continue to comply with trial proceduresDisease progression that requires discontinuation of the trial or results due to inability to continue to comply with trial proceduresWithdrawal of consentLoss of follow-up

Participants also may be withdrawn if the regulatory authorities terminate the study prior to its planned end date. If the participant is withdrawn due to an adverse event, the treating dentist will arrange for follow-up visits or telephone calls until the adverse event has resolved or stabilized.

### Compliance With Trial Treatment

The follow-up visits of the individual are important for the trial. Compliance to visit the dental clinic at designated intervals is done by telephonic and email reminders to the individuals. If the individual has missed the appointment or wants to reschedule, then it is rescheduled within +/– 2 days. If the individual misses two rescheduled appointments, then it is referred as noncompliance. The individual will be withdrawn from the study. However, if the individual completes 6 months and becomes noncompliant for the next 6 months, the person’s time of participation in the trial will be counted and will be used for analysis.

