### Analysis Population and Missing Data

We will report reasons for withdrawal for each randomization group and compare the reasons qualitatively. The effect that any missing data might have on results will be assessed via sensitivity analysis of augmented data sets. Dropouts will be included in the analysis by using multiple imputation methods for missing data. Excluding patients from the analysis who violated the research protocol (did not get their intended treatment) can have significant implications that impact the results and analysis of a study. If the attrition loss is less than 15%, a per protocol analysis will be carried out; otherwise, “intention to treat” will be performed.

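### The withdrawal rules do not separate stopping allocated treatment from stopping outcome measurement, so pain and EMG data can be lost for reasons that may relate to pain or to known allocation

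*Protocol article*

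**What the plan says.** All references are to the protocol article.

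- **Compliance With Trial Treatment.** A missed visit may be rescheduled within 2 days either way. Then: "If the individual misses two rescheduled appointments, then it is referred as noncompliance. The individual will be withdrawn from the study". One exception follows: "if the individual completes 6 months and becomes noncompliant for the next 6 months, the person’s time of participation in the trial will be counted". Such a patient's data then enter the analysis.
- **Retention.** Here "the treating dentist may discontinue an individual from the trial at any time if they consider it necessary for any reason". The listed reasons include ineligibility found later, significant protocol deviation, significant noncompliance, and disease progression that either requires discontinuation or leaves the patient unable to comply with trial procedures. Contact after withdrawal is described for one case only, an adverse event, where "the treating dentist will arrange for follow-up visits or telephone calls until the adverse event has resolved or stabilized".
- **Blinding.** The article states that "neither the treating dentist or patients are blinded".
- **Data Collection Methods.** Once a person is enrolled or randomised, "the study site will make every reasonable effort to follow the individual for the entire study period", given there as 12 months. Loss to follow-up is projected at no more than 5% per year.
- **Outcomes.** "The outcome measurements will be made at baseline and at the time points of 24 hours, 7 days, 28 days, and 3 months".
- **Analysis Population and Missing Data.** "Dropouts will be included in the analysis by using multiple imputation methods for missing data". The section also plans sensitivity analyses and a report of withdrawal reasons by randomised group.

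**The concern.** Stopping the allocated treatment and stopping measurement are different events, and the article describes both with the same words: discontinued or withdrawn from the trial or study. A site that reads the missed-appointment rule literally has no reason to seek VAS or EMG at the remaining visits. A patient withdrawn early can lose the 28-day and 3-month values even if willing to attend later.

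The reasons for withdrawal may be linked to the result. The primary objective is pain reduction, and progression or noncompliance may go with pain. Patients and treating dentists know the allocation. Under Recruitment, patients are offered the trial after opting for prosthetic rehabilitation, while controls receive symptomatic treatment and counselling, so attendance could plausibly differ by arm. If it does, the patients with a 3-month value are no longer the groups that randomisation formed. An analysis plan cannot restore measurements that the protocol did not have sites collect.

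**Working it through.** **1. The passages side by side.**

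| Event | What ends | Mandatory? | Outcome measurement afterwards |
|---|---|---|---|
| Two missed rescheduled appointments | Study participation | Yes | None stated |
| Noncompliance, protocol deviation, late-found ineligibility (dentist's decision) | Trial participation | No | None stated |
| Progression that requires discontinuation or prevents compliance (dentist's decision) | Trial participation | No | None stated |
| Withdrawal for an adverse event | Trial participation | No | Contact until the event resolves or stabilises; no VAS or EMG mentioned |

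Only the first row is an automatic rule. No row separates treatment from measurement.

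**2. The 6-month exception.** Outcomes, Participation Timeline and Table 1 place the last outcome visit at 3 months. On that schedule nobody can complete 6 months of outcome visits and then default, so the exception protects no one. It fits only the 12-month horizon used in Data Collection Methods, Table 3 and Data Monitoring. On that horizon it still leaves out anyone who becomes noncompliant before 6 months.

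**3. Possible size, as an illustration only.** The article gives no figure for bias from withdrawal, so there is none to reproduce. Assume a normally distributed change score within an arm, loss of exactly the worst fraction p of that arm, and no imputation. The mean of those who remain moves by

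shift = φ(z_p) / (1 − p), in SD units.

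- p = 5%: 0.1031 / 0.95 = 0.109 SD.
- p = 10%: 0.1755 / 0.90 = 0.195 SD.
- Same p in both arms, same SD: the shifts cancel and the difference is unbiased.
- Loss in the other arm: same size, opposite direction.

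**4. Scaling to the projected loss.** If the 5% annual projection also covers withdrawals (the article does not say so) and is spread evenly over time, 3 months gives 5% × 3/12 = 1.25% overall. If all of it fell in one of two equal arms, that arm would lose 2.5%, and the shift would be 0.0584 / 0.975 = 0.06 SD.

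**5. A less extreme mechanism.** Assume a true difference of 0.50 SD and one common poor-response threshold c, below which patients leave either arm and are excluded. The observed difference is

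d + φ(c − d)/(1 − Φ(c − d)) − φ(c)/(1 − Φ(c)).

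- 5% overall loss (7.4% control, 2.6% intervention): 0.41 SD.
- 14% overall loss (19.4% control, 8.6% intervention): 0.33 SD.

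These are assumed scenarios, not estimates for this trial. None is set against the effect size of 0.77 in Sample Size, because that figure was derived for masticatory-muscle EMG activity. The article gives no effect size for VAS pain.

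**The case against.** **Progression.** A reader might infer that any patient whose disease progresses is removed. The text does not support that. The dentist may discontinue a patient, and only for progression that requires discontinuation or prevents compliance. Ordinary worsening of pain triggers nothing. This stands.

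**Silence on later data.** After a discontinuation under Retention, the article is silent on measurement, and a fuller protocol might cover it. That is fair for Retention. It does not answer the missed-appointment rule, which plainly ends participation.

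**Unavoidable loss.** A patient who has missed two rescheduled appointments despite reminders has already lost those measurements under any rule. The avoidable loss is the later visits of early non-attenders. This stands, and it narrows the point.

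**Conflict with Data Collection Methods.** A reader might call the two sections opposites. Reasonable effort to follow is compatible with giving up after repeated failures, so they are in tension, not flat contradiction.

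**Imputation.** Multiple imputation, with earlier VAS values to draw on, and the sensitivity analyses give real partial cover. Standard imputation, however, assumes that the observed data explain the missingness, and a patient who leaves because of a later change in pain breaks that assumption. The same section also makes per protocol the analysis when attrition is below 15%. That is a separate question, but it means imputation cannot simply be relied on.

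**Direction.** A reader might infer that controls drop out more and that the benefit is therefore hidden. Controls do receive active care, and nothing in the article settles which arm would lose more.

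**Conclusion.** The point holds in limited form. One mandatory rule and one broad discretion end participation in the trial without saying that outcome measurement continues. Losses may therefore relate to pain or to known allocation, and the imputation plan covers this only in part. The 6-month exception has no effect on the 3-month schedule; whether it has a purpose depends on a horizon that the article leaves unsettled.

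Neither the size nor the direction of bias can be derived from the documents. The figures of 0.11 and 0.195 SD rest on normality, perfect selection of the worst tail, loss in one arm only and no imputation. Scaled to the projected loss over 3 months, the same formula gives about 0.06 SD at worst. With equal selective loss in both arms it gives zero. A reader might conclude that the pain comparison is bound to be selected on its own outcome; the text shows only that it can be. This should be fixed, but it does not by itself invalidate the design.

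**What to change.** In Retention and Compliance With Trial Treatment:

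- Define two separate events: discontinued allocated treatment, and withdrew consent to follow-up.
- State that noncompliance, missed visits, protocol deviation, late-found ineligibility or progression do not by themselves end outcome collection.
- Continue to seek VAS and EMG at every remaining scheduled visit unless consent is withdrawn or the patient is truly lost.
- Record the date of, and reason for, treatment discontinuation.
- Replace the 6-month data-retention rule with use of all data collected.

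Then reconcile these two sections with Data Collection Methods and with Analysis Population and Missing Data, on whichever follow-up horizon (3 or 12 months) the sponsor confirms. The change concerns measurement only and leaves decisions on treatment where they are.

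The cost is protocol wording, site instruction and some extra effort in contacting poor attenders. The visits are already scheduled.
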